### Outcome measurement

2.3

The *H pylori* infection is diagnosed by 1 or more of the following methods: the rapid urease test, the UBT or a histological examination. Two specimens from the gastric corpus and antrum will be taken during an endoscopy for the rapid urease test (Pronto Dry New; Medical Instruments Corp., Herford, Germany) or a histological assessment using Giemsa staining. A UBT (UBiT-IR 300; Otsuka Pharmaceutical Co., Ltd, Tokyo, Japan) measuring exhalation of ^13^CO_2_ before and 30 minutes after ingestion of 75 mg of ^13^C-marked urea will be performed. An initial breath sample will be obtained after at least an 8-hour fasting period (overnight fasting). The UBT after eradication of *H pylori* will be performed at least 4 weeks after the eradication therapy has ended. Delta over baseline >2.5% will be considered positive. Subjects who take medications that may affect the outcome of the UBT (e.g., PPI, H2RA, antibiotics) after the end of the eradication regimen will be tested at least 4 weeks after stopping these medications (the wash-out period is at least 4 weeks). In this case, the routine follow-up period for the 2nd visit (6 weeks after enrollment) will be prolonged assuming no violation of the study protocol has taken place.

All the subjects will be educated about common adverse events related to the eradication medications, and they will be asked to submit self-report questionnaires about adverse events related to the eradication medications at the 1st visit (2 weeks after enrollment, after ending the eradication regimen) and at the 2nd visit (6 weeks after enrollment, for UBT checking). The severity of the adverse events is defined as “mild” (transient and well tolerated), “moderate” (causing discomfort and partially interfering with daily activities), or “severe” (causing considerable interference with daily activities) and will be taught to the subjects for reporting as described above.^[20]^ Potential adverse events will be monitored by the research staff for 3 months after enrollment. Information about adverse events related to the eradication medications will also be gathered through interviews conducted by the doctors and independent staff at the 1st and 2nd visits. Compliance with the eradication regimen will be checked at the 1st visit by independent staff.

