### Randomization and blinding

2.4

Eligible patients will be approached during their routine gastroenterology unit visit by the research team for recruitment. A single independent staff member will prepare the randomization sequence, which will be accomplished using a block design and a block size of 4. Randomization of a block will be done by means of a random-number chart. This study is an open-label trial due to the difference in administration method for each arm. The modified quadruple therapy group will have amoxicillin twice a day, whereas the bismuth-containing quadruple therapy group will have tetracycline 4 times a day. Therefore, doctors and participants will be aware of the drugs that are prescribed. However, only the rate of eradication success, adverse events, and compliance with the therapies will be considered outcomes of this trial, and it is believed that an open-label design in itself will not influence the procedure or results of the trial.

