A recent study in Korea has shown that modified quadruple therapy has rates of eradication success and adverse events comparable to those of concomitant therapy.^[19]^ Characterizing the regional antibiotic resistance profile is important for *H pylori* eradication because antibiotic resistance is the chief cause of treatment failure. However, the study above did not explore antibiotic resistance profiles, making it difficult to interpret its results. A previous study has also shown that modified quadruple therapy is comparable to bismuth-containing quadruple therapy as a rescue regimen for patients with at least 2 consecutive treatment failures.^[20]^ Additionally, modified quadruple therapy has been shown to have high eradication success even in subjects with amoxicillin, metronidazole, or clarithromycin resistance, and this therapy has fewer adverse events and higher compliance than does bismuth-containing quadruple therapy.^[20]^

This study will compare the efficacy and safety of modified quadruple therapy and bismuth-containing quadruple therapy as well as presenting the phenotypic and genotypic antibiotic resistance profile of *H pylori*. The strength of this study resides in providing evidence regarding the efficacy and safety of using modified quadruple therapy as a 1st-line regimen in different regions of Korea compared to previous reports (a previous study was conducted in Seoul as a single center study; however, we will recruit patients in Gangwon and Gyeonggi provinces) and additionally, in providing evidence on the use of bismuth-containing quadruple therapy as a 1st-line treatment, which has been scarce as a 1st-line treatment in Korea. Moreover, with the comparative results of the antibiotic-susceptibility gold standard ‘agar dilution’ method vs. DNA sequencing of the clarithromycin resistance point mutations in the 23S rRNA of *H pylori*, it will be possible to interpret the outcome of this study in light of the antibiotic resistance profiles of *H pylori* including the unknown clinical significance of point mutations, such as G2141A, A2144T, or T2182C.

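### The stated belief that open-label treatment will not affect the results holds for the breath test but not for self-reported, unblinded adverse events, and only in part for compliance

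*Protocol article*

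**What the plan says.** The protocol article, section 2.4 (Randomization and blinding), explains that the trial is open label because the regimens are taken differently, and accepts that "doctors and participants will be aware of the drugs that are prescribed". It then argues that this is harmless: "only the rate of eradication success, adverse events, and compliance with the therapies will be considered outcomes of this trial", and so "it is believed that an open-label design in itself will not influence the procedure or results of the trial".

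Section 2.3 (Outcome measurement) says how each of the three outcomes is obtained:

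- **Eradication:** a urea breath test at least 4 weeks after treatment, positive above a delta-over-baseline cut-off of 2.5%.
- **Adverse events:** subjects are first taught the common ones, then asked to "submit self-report questionnaires about adverse events related to the eradication medications" at both follow-up visits. They are taught the grades (mild, moderate, severe), which turn on tolerability and interference with daily life. The same kind of information "will also be gathered through interviews conducted by the doctors and independent staff at the 1st and 2nd visits". Research staff also monitor potential adverse events for 3 months after enrollment.
- **Compliance:** checked at the first visit by independent staff.

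Section 2.6 (Statistical analysis) compares eradication, compliance and adverse event rates between the arms, with two-tailed P<.05 as the threshold for all tests. It also makes compliance below 80% a violation that removes a subject from the per-protocol set.

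**The concern.** The only reason given for regarding the open label as harmless is the nature of the three outcomes. If that reason fits just one of them, the plan claims a protection that its design does not provide.

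Safety is part of the stated aim alongside efficacy, and adverse event rates are to be tested between arms. If subjects or doctors who know the regimen are readier to report an event, grade it higher or blame the drugs in one arm, the comparison mixes a drug effect with a reporting effect. The final analysis has no way to separate the two. To the extent that an event judged unrelated is left off the report, restricting or widening the analysis later cannot bring it back. That is why the matter belongs in the protocol and not in the interpretation of the results.

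**Working it through.** **1. Does the reason given in section 2.4 fit each outcome as measured in section 2.3?**

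| Outcome | Who produces the value | Knows the arm? | Judgement involved | Does the reason fit? |
|---|---|---|---|---|
| Eradication | Breath-test instrument, fixed cut-off | Not relevant to the reading | Little | Yes, for the reading |
| Adverse events | Subject (questionnaire, severity grade); doctors and independent staff (interview) | Subjects and doctors: yes. Independent staff: not stated | Noticing, grading, attributing to the drugs | No |
| Compliance | Checked by independent staff | Subject: yes. Staff: not stated | Depends on the method, which the article does not give | Only in part |

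For adverse events, knowledge of the arm can enter at three places: whether the subject reports, how severe the subject calls it, and whether it is regarded as drug-related. The third arises because the questionnaires and the interviews are both described as covering events related to the eradication drugs.

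For compliance, the link to efficacy runs through the 80% rule. If compliance were judged differently by arm, different subjects would leave the per-protocol set, although the breath-test reading itself would be untouched.

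**2. The plan's own figure.** The illustration below uses the planned 100 per arm, which can be reproduced. With 96.2% eradication in both arms, a margin of 8 points, one-sided 0.025 and 80% power:

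n = 2 × 0.962 × 0.038 × (1.960 + 0.842)² / 0.08² = 89.7, rounded up to 90; then 90 / 0.90 = 100 per arm.

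The concern does not dispute this number.

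**3. Illustration of sensitivity.** The documents give no adverse event rate, no size of reporting shift and no named test for adverse events (Fisher's test is named for baseline categorical variables). All three are therefore assumptions. Let the true rate be p in both arms and let reporting raise one arm to p + d. With b(·; n, p) the binomial probability,

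P(significant) = Σᵢ Σⱼ b(i; n, p) · b(j; n, p + d) · 1[two-sided Fisher P for (i, j) < 0.05].

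Results with n = 100 per arm:

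| True rate p | d = 0 | d = 5 points | d = 10 points | d = 15 points |
|---|---|---|---|---|
| 20% | 3.3% | 10.1% | 31.3% | 60.8% |
| 30% | 3.5% | 8.9% | 26.3% | 53.5% |
| 40% | 3.6% | 8.9% | 26.1% | 53.0% |
| 50% | 4.0% | 9.2% | 26.1% | 53.0% |

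If the planned 10% dropout leaves 90 per arm, the 40% row becomes 3.7%, 7.9%, about 22% and 44.8%. At 100 per arm, an observed 40% against 55%, or 30% against 45%, is the smallest gap from that base that reaches P<.05.

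These are rejection probabilities for a chosen difference. They show how much reporting shift the comparison could absorb; they do not predict that a shift of any given size will occur.

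**The case against.** Several points on the other side are sound.

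- **The wording is hedged.** The plan discloses the open label, explains it and states a belief. It does not say that bias is impossible. Even so, this belief is the only justification offered, and it covers all three outcomes.
- **Compliance.** A reader might infer that compliance is as exposed as adverse events. The documents do not support that. Independent staff check it, nothing shows that they know the arm, and a difference between amoxicillin twice daily and tetracycline four times daily may be a real property of the regimens. What remains is that independent is not stated to mean blinded.
- **Lost events.** A reader might infer that unrelated events are never written down. That is not established. The form is not shown, independent staff also interview at both visits, and the 3-month monitoring of potential adverse events carries no relatedness limit. But the article does not say that this monitoring feeds the between-arm comparison.
- **Direction of bias.** A reader might take the Discussion's remark that "this therapy has fewer adverse events and higher compliance than does bismuth-containing quadruple therapy" as the investigators' forecast for this trial. It reports an earlier study of rescue treatment after at least two failures. It shows that such an expectation is available to the investigators, not that subjects are told of it or that bias will favour the modified arm.
- **Size.** A reader might infer that a safety difference would be produced by expectation alone. The rates and shifts are assumed, so that is a possibility and no more.
- **Efficacy.** The sample size rests on eradication, whose reading is largely protected.

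None of this rescues the section 2.4 argument for adverse events, where subjects and doctors who know the drugs supply the data.

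**Conclusion.** The point holds for adverse events. Section 2.4 extends to all three outcomes a protection that section 2.3 supports only for the breath-test reading. For compliance it holds in a weaker form: the staff's blinding is unstated, a true regimen effect is plausible, and the 80% rule gives any arm-dependent assessment a route into the per-protocol efficacy comparison.

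The size cannot be derived from the documents. Under the assumptions of equal true rates of 40%, 100 per arm and a two-sided Fisher test, a reporting shift of 5, 10 or 15 points yields P<.05 in about 9%, 26% or 53% of trials, against 3.6% with no shift. The sample size is not affected. The change should be made because the safety comparison is part of the aim and the correction is cheap; the eradication measurement does not depend on it.

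**What to change.** **In section 2.3:**

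1. Use one identical checklist in both arms that lists the expected effects of every drug in either regimen.
2. Record every event whatever its presumed cause, and assign relatedness afterwards as an attribute of the event.
3. Base the between-arm comparison on all recorded events, with rates restricted to related events as secondary.

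**In section 2.4:** limit the sentence on open-label influence to the breath-test outcome. State that differences in adverse events and compliance are open to reporting bias and will be interpreted with that limit.

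Interviewers need not be kept unaware of allocation. Subjects know their drugs and can reveal them, and the independent staff check compliance at the same first visit, so masking would be hard to maintain.

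**Cost:** revised questionnaire wording and a short amendment, with no change to visits or sample size. More background events will be recorded, so adverse event rates will look somewhat higher in both arms. Recruitment was planned from August 2018 and the article appeared in November 2018, so the form may change during the trial. In that case the form version should be noted for each subject.

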### Phenotypic and genotypic antibiotic resistance test

2.5

For the subjects who will prospectively undergo endoscopic examination with the rapid urease test or a histological examination to determine *H pylori* infection, 1 biopsy specimen from the gastric corpus or antrum will be cultured with an agar dilution test to assess phenotypic antibiotic resistance, and 1 specimen will be used to sequence the 23S rRNA gene in clarithromycin-resistant strains to assess genotypic antibiotic resistance. For the subjects who already underwent endoscopic examination or who were diagnosed with *H pylori* infection using the UBT, antibiotic resistance tests will be omitted.

The biopsy specimen will be cultured and maintained on brucella broth agar supplemented with 5% sheep blood and containing vancomycin (10 μg/mL), trimethoprim (5 μg/mL), amphotericin B (5 μg/mL), and polymyxin B (2.5 IU) under microaerophilic conditions (5% O_2_, 10% CO_2_, 85% N_2_) at 37°C for 3 to 7 days. All isolates will be stored in brucella broth supplemented with 15% glycerol at −70°C. A culture will be considered positive if 1 or more colonies are Gram-negative and positive for urease, oxidase, and catalase with a spiral/curved rod morphology. We will obtain 1 isolate per subject, and all of the stored isolates will be thawed and passaged for the agar dilution test.^[21]^

Thawed isolates will be inoculated onto Mueller-Hinton agar supplemented with 5% defibrinated sheep blood for 48 hours. Bacterial suspension adjusted to 1 x 10^7^ colony-forming units (equivalent to that of a No.2 McFarland opacity standard by spectrophotometry) will be inoculated directly onto an antibiotic-containing agar dilution plate at various concentrations. After 72 hours of microaerophilic incubation, the minimal inhibitory concentrations (MIC) of amoxicillin, clarithromycin, metronidazole, tetracycline, and levofloxacin will be determined by the 2-fold agar-dilution method. All 3 susceptibility tests will be performed for each sample. The breakpoint of MICs will be defined according to the criteria of the National Committee for Clinical Laboratory Standards (MIC value >0.5 μg/mL (amoxicillin), >1 μg/mL (clarithromycin), >8 μg/mL (metronidazole), >4 μg/mL (tetracycline), and >1 μg/mL (levofloxacin)), and ATCC 43504 (ATCC, Manassas, VA) will be used as the reference strain.^[22,23]^

*H pylori* genomic DNA will be extracted from biopsied tissue with the MagNA Pure 96 DNA and Viral NA Small Volume Kit (Roche Diagnostics, Forrenstrasse, Switzerland) according to the manufacturer's instructions. We will examine the nucleotide sequence of domain V in the 23S rRNA gene of *H pylori* by amplifying approximately the first 300 bp to detect mutations at positions 2141, 2142, 2143, 2144, and 2182. Nucleotide sequencing of the amplified DNA will be performed using an ABI 3730 DNA Analyzer (Applied Biosystems, Foster City, CA) with BigDye Terminator V3.1 according to the manufacturer's instructions. All end-point PCR reactions will be visualized with agarose gel electrophoresis, and all sequencing work will be performed by a commercial expert agency (Samkwang Medical Laboratories, Seoul, Korea).

### Statistical analysis

2.6

The sample size was calculated by using an α-error <0.05 and a β-error <0.2 for a 2-tailed significance test. The calculated number of subjects required for the trial is 100 in each arm, which was determined by assuming an eradication rate of 96.2% from treatment with bismuth-containing quadruple therapy for 14 days as seen in a previous study in Korea (per-protocol (PP) analysis), an equivalence margin of 8%, and a dropout rate of 10%.^[24]^

For the intention-to-treat (ITT) analysis, all participants who take at least the 1st dose of prescribed medications will be included and assessed and for the modified ITT analysis, all participants who take at least the 1st dose of prescribed medications and who are in the posttreatment *H pylori* status will be included and assessed. For the PP analysis, only those who maintain and complete treatment with the prescribed medications without violating the regulations (violation is <80% medication compliance; poor adherence to medication is defined as taking less than 80% of what is prescribed) will be included and assessed (Fig. 1).

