**Figure 1 F1:**
[figure not shown]
Flow chart of the study. ITT = intention-to-treat, n = number, PP = per-protocol.

Continuous variables will be expressed as the mean ± standard deviation. Categorical variables will be expressed as numbers and percentages. First, we will compare the baseline characteristics of enrolled subjects (age, sex, smoking, alcohol use, reason for *H pylori* eradication) using Student *t* test and Fisher exact test for continuous and categorical variables, respectively. The Mann–Whitney test will be alternatively used if a continuous variable does not have a normal distribution. We will then perform ITT, modified ITT, and PP analyses to compare the eradication success rates, compliance with therapies, and adverse event rate between the 2 arms. Subgroup analyses will be performed according to the reason for eradication and the antibiotic resistance profile of the *H pylori* isolate. A *P* value <.05 (2-tailed) will be adopted as the threshold for statistical significance for all tests. All of the analyses will be performed using SPSS version 24.0. (SPSS Inc., Chicago, IL).

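### At 90 evaluable patients per arm the stated alpha and beta are not both met: interval methods that hold the 2.5% one-sided error have about 64% to 69% power even for non-inferiority

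*Protocol article*

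**What the plan says.** All inputs stand in section 2.6 (Statistical analysis) of the protocol article. On error rates: "The sample size was calculated by using an α-error <0.05 and a β-error <0.2 for a 2-tailed significance test". On the result: "The calculated number of subjects required for the trial is 100 in each arm". It is derived by "assuming an eradication rate of 96.2% from treatment with bismuth-containing quadruple therapy for 14 days", a per-protocol figure from an earlier Korean study, with "an equivalence margin of 8" percent and 10% dropout. No separate rate is given for modified quadruple therapy.

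Later in the same section, a two-tailed P value below .05 is set as the threshold for all tests. The article does not name the sample-size formula, or the interval or test by which the difference in eradication rates will be judged against the margin.

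**The concern.** A normal-approximation sample size is least reliable when the success rate is close to 100%. Here two features work against it.

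- If both regimens eradicate at 96.2%, an arm of 90 expects only 3.4 failures, and has fewer than five in 74% of trials.
- The formula that gives 90 uses the variance at 96.2% in both arms. At the margin the modified arm would be at 88.2%, where its binomial variance is almost three times as large.

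An analysis that mirrors the formula may then accept a regimen that is 8 points worse more often than 2.5% of the time. An analysis that holds 2.5% may have less than the stated 80% power. Readers of the protocol would expect a conclusive result more often than the design can give one.

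**Working it through.** **Inputs (section 2.6).** Two-tailed alpha 0.05, taken as one-sided 0.025 at the margin; power 0.80; control rate 0.962; margin 0.08; dropout 10%; 100 per arm. Assumption: a true difference of zero, since only one rate is given.

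**Reproducing the plan's figure.** Unpooled non-inferiority formula:

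n = (1.960 + 0.842)² × [0.962 × 0.038 + 0.962 × 0.038] / 0.08² = 7.849 × 0.073112 / 0.0064 = 89.7, so 90.

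With dropout, 90 / 0.90 = 100. This matches. The other readings tried do not:

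| Reading | Evaluable per arm | With 10% dropout |
|---|---|---|
| Non-inferiority, one-sided 0.05 | 71 | 79 |
| Equivalence, two one-sided tests at 0.05 | 98 | 109 |
| Equivalence, two one-sided tests at 0.025 | 121 | 135 |
| Superiority, 96.2% vs 88.2% | 176 | – |

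**Where the approximation is weak.** Expected failures per arm with no true difference: 90 × 0.038 = 3.42. Variance at the margin: 0.882 × 0.118 = 0.1041, against 0.962 × 0.038 = 0.0366, a ratio of 2.85.

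**Exact operating characteristics.** For every pair of success counts, determine whether the lower limit of the 95% interval (or the equivalent score test) lies above -0.08, and sum the product of the two binomial probabilities over the pairs that pass. Power is taken at 96.2% in both arms, and the error at 88.2% (modified) versus 96.2% (control).

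| Method | Error, n = 90 | Power, n = 90 | Error, n = 100 | Power, n = 100 |
|---|---|---|---|---|
| Wald | 3.4% | 78.5% | 3.4% | 82.1% |
| Newcombe | 2.5% | 69.2% | 2.1% | 71.4% |
| Farrington-Manning | 2.2% | 68.7% | 2.1% | 71.4% |
| Miettinen-Nurminen | 1.9% | 64.5% | 2.1% | 71.4% |

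The n = 100 columns suppose no dropout at all.

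**Sensitivity to the rate, n = 90.** At 95% in both arms, power is 69% (Wald), 62% (Newcombe) and 60% (Farrington-Manning). At 97% it is 85%, 75% and 75%, with a Wald error of 3.6%. At 98%, Newcombe and Farrington-Manning reach 84%, and the Wald error is 4.0%.

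**Two-sided equivalence, n = 90.** Requiring both limits inside ±8 points with the same 95% intervals, power is 57% (Wald), 39% (Newcombe), 38% (Farrington-Manning) and 30% (Miettinen-Nurminen).

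**The case against.** **The Wald analysis is an inference.** Planning with a normal-approximation formula does not commit anyone to a Wald interval, and the choice of interval is commonly left to an analysis plan, which is not shown here. This stands. A reader might infer that the trial will be analysed with a test that overspends its error rate; the article does not say so, and the absence of a named interval is not itself a fault. What remains is the stated pair of error rates: none of the four methods above meets both at 90 evaluable, so choosing among them elsewhere would not make both figures true.

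**The sample size is correct arithmetic.** This also stands: 100 follows from the inputs. The fault lies in the power that this number delivers.

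**The normal approximation does not collapse.** A reader might say that it breaks down. That goes too far: Wald power is within 2 points of 80%, and its error exceeds nominal by 0.9 points. The figure of three to four failures per arm holds only when both regimens are at 96.2%. At the margin the modified arm expects 90 × 0.118 = 10.6.

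**A one-sided alpha of 0.05 would restore the power.** With that alpha and 90 per arm, Newcombe has 82% and the score methods 79%. But this contradicts the two-tailed 0.05 in section 2.6 and would give 79 per arm, not 100.

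**The margin is called an equivalence margin.** This question comes first and is the larger one. The non-inferiority figures are the sponsor's best case.

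**Conclusion.** The point holds. On the non-inferiority reading, at the planning rate and 90 evaluable per arm, power with a method that holds the one-sided 2.5% level is 64.5% to 69.2%. The type II error is therefore about 31% to 36%, against the stated limit of 20%. With no dropout it is still about 29%. The Wald limit comes close to the stated power only by letting the error rise to 3.4%.

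This rests on four assumptions: two-tailed 0.05 read as one-sided 0.025; no true difference; 96.2% in both arms; and 90 evaluable. Because counts are discrete, power moves in steps with the number evaluable, so the figures are specific to 90. Newcombe holds its level only approximately: its largest error over control rates from 90% to 99.9% is 2.58%. If the true rate were near 98%, the stated power would be reached with a method that holds its level. At 97% or below, among the rates checked, it would not.

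For scale, about 115 to 121 evaluable per arm would give 80% (80.05% at 115 and 82% at 121, for Newcombe and both score methods). The documents do not support the inference that the trial must be enlarged; an honest statement of power is enough.

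**What to change.** Keep 100 per arm. In section 2.6, in one statement:

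1. Say whether the aim is non-inferiority or two-sided equivalence.
2. Name one interval for the difference in eradication rates that holds its level. If non-inferiority is meant, this could be the Newcombe 95% interval with its lower limit compared with -8 points.
3. Replace the 80% power by the figure for that method at 90 evaluable per arm: about 69% for Newcombe, or about 64% if Miettinen-Nurminen is chosen. One figure does not serve both. If equivalence is meant, the corresponding figures are 39% and 30%.

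The cost is a sentence or two and a lower stated power; some software needs a short macro for the interval. No extra patients are needed.

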## Discussion

3

The clarithromycin-containing triple regimen for *H pylori* eradication is no longer acceptable due to a high clarithromycin resistance in Korea, and concomitant therapy or bismuth-containing quadruple therapy is recommended as an alternative regimen.^[8,9,12,13]^ However, Korea is classified as a region with high clarithromycin (>15%) and metronidazole resistance (>30%).^[9,16]^ Data on the trends over time have shown a constant acceptable eradication success rate for bismuth-containing quadruple therapy as a 2nd-line regimen;^[24,26,27]^ however, there is a paucity of data on its use as a 1st-line regimen in Korea.^[28]^ Moreover, there is no definite 2nd-line or 3rd-line rescue regimen for patients who do not respond to the above therapies.^[17]^ Fluoroquinolone- and rifabutin-containing regimens or a combination of bismuth with different antibiotics is the remaining empirical option.^[8,17]^ However, the antibiotic resistance rates in Korea of ciprofloxacin, levofloxacin, and moxifloxacin are reported to be up to 38.2%, 37.7%, and 34.6%, respectively, which are higher than those previously reported.^[15,17,29]^ Cross-resistance between rifabutin and rifampin is a serious concern in tuberculosis prevalent countries such as Korea due to concerns that overuse may increase the prevalence of rifabutin-resistant mycobacteria in the community.^[17]^ Antibiotic susceptibility guided treatment is beginning to receive more attention; however, it is not widely available at all institutions.^[17]^

In a meta-analysis of Korean studies, concomitant therapy showed a higher eradication rate than sequential therapy.^[30]^ Though there has been no published data on its trends over time, the continuous eradication success of concomitant therapy can be demonstrated through the enrolled studies in a recent systematic review of Korean studies.^[31]^ However, concomitant therapy is not recommended in regions with high metronidazole resistance, and the resistance rate of metronidazole has been reported to be as high as 66% in Korea.^[9,16]^ Moreover, dual clarithromycin and metronidazole resistance undermines the efficacy of concomitant therapy.^[18]^

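### The 100 per arm is a one-sided non-inferiority sample size; for the equivalence margin that section 2.6 names, power is about 60% (95% CI) or 75% (90% CI), not 80%

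*Protocol article*

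**What the plan says.** Section 2.6 (Statistical analysis) gives the whole calculation in two sentences. The error rates are: "The sample size was calculated by using an α-error <0.05 and a β-error <0.2 for a 2-tailed significance test". The number and the remaining inputs follow: "The calculated number of subjects required for the trial is 100 in each arm, which was determined by assuming an eradication rate of 96.2"%, identified as a per-protocol figure from a Korean study of the 14-day bismuth regimen, together with "an equivalence margin of 8%, and a dropout rate of 10"%.

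No eradication rate is given for modified quadruple therapy. The Introduction states the aim as comparing the two regimens. Later in section 2.6, a two-tailed 5% threshold is applied to every test. The article writes out neither an equivalence nor a non-inferiority hypothesis, and gives no confidence-interval rule to go with the 8%.

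**The concern.** An equivalence margin has two sides. To conclude equivalence, the confidence interval for the difference must exclude both −8 and +8 points. When the true rates are equal, the interval can miss on either side, so the type II error is shared between two bounds and the sample size formula must use β/2. The printed number appears to use the full β on one bound, which is a non-inferiority calculation.

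If so, section 2.6 combines the name of one objective with the sample size of another, and the 80% power belongs only to the second. At stake is which conclusion 100 per arm can support. Someone who takes the word equivalence at face value would expect a truly equivalent regimen to miss the criterion at most 1 time in 5; the actual figure is higher.

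**Working it through.** **Inputs, all from section 2.6:** α = 0.05, 2-tailed (z = 1.960); β = 0.2 (z = 0.842); control rate p = 0.962; margin m = 0.08; dropout 10%; 100 per arm. **Assumption:** the rate for modified quadruple therapy is not stated and is taken as 0.962, a true difference of zero. This is the case most favourable to equivalence.

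**Step 1. Reproduce the plan's figure.** Non-inferiority at one-sided 0.025:

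n = (z₁₋α + z₁₋β)² × 2p(1−p) / m²
= (1.960 + 0.842)² × 2 × 0.962 × 0.038 / 0.08²
= 89.7, so 90 evaluable; 90/0.9 = **100**. Exact match.

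**Step 2. Try the other standard calculations, each with the 10% dropout.**

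| Calculation | Evaluable per arm | Randomised per arm |
|---|---|---|
| Non-inferiority, one-sided 0.025 | 90 | 100 |
| Non-inferiority, one-sided 0.05 | 71 | 79 |
| Equivalence, 0.05 per side (90% CI) | 98 | 109 |
| Equivalence, 0.025 per side (95% CI) | 121 | 135 |
| Difference test, 96.2% vs 88.2%, two-sided | 176 | 196 |
| Difference test, 96.2% vs 88.2%, one-sided | 138 | 154 |

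The equivalence rows use the Step 1 formula with β/2 = 0.1 (z = 1.282):

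- 95% CI: (1.960 + 1.282)² × 0.073112 / 0.0064 = 120.03, so 121; 121/0.9 = 134.4, so 135.
- 90% CI: (1.645 + 1.282)² × 0.073112 / 0.0064 = 97.8, so 98; 98/0.9 = 108.9, so 109.

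With a continuity correction, the difference tests need more: 223 two-sided and 180 one-sided. Only the first row gives 100.

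**Step 3. Power with 90 evaluable per arm.**

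SE = √(2 × 0.962 × 0.038 / 90) = 0.0285; m/SE = 2.807.

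- Non-inferiority, one-sided 0.025: Φ(2.807 − 1.960) = Φ(0.847) = 0.801.
- Equivalence, 95% CI: 2Φ(0.847) − 1 = **0.603**.
- Equivalence, 90% CI: 2Φ(2.807 − 1.645) − 1 = 2Φ(1.162) − 1 = **0.755**.

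**Step 4. Exact check.** With rates this close to 100% the normal approximation is optimistic. Enumerating all binomial outcomes at n = 90 and p = 0.962 in both arms gives:

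| Criterion | Normal approx. | Exact, Wald limits | Exact, Newcombe limits |
|---|---|---|---|
| Non-inferiority, one-sided 0.025 | 80% | 79% | 69% |
| Equivalence, 95% CI | 60% | 57% | 39% |
| Equivalence, 90% CI | 75% | 72% | 64% |

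Equivalence is below 80% in every column.

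**The case against.** **The plan may simply have meant non-inferiority.** This is the strongest reply. The aim is only to compare, one phrase carries the whole equivalence reading, and an upper limit of 96.2% + 8% = 104.2% cannot be reached by a rate. On that reading the sample size and β are right and one word is wrong. This stands, and it is why the point is a mismatch between hypothesis and power rather than an arithmetic error. It does not remove the need for a correction, because equivalence is the only term section 2.6 attaches to the 8%.

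**The 60% depends on a convention.** This also stands. The 2-tailed 5% wording points to a 95% CI, but no interval rule is stated. Conventional two one-sided tests at 5% use a 90% CI and give 75%. The shortfall is therefore about 5 to 20 points.

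**Equivalence at 5% per side needs 98, close to 100.** That holds only without dropout. If all 100 per arm were evaluable, power with a 90% CI would be 81%, but section 2.6 states 10% dropout, and with it the number is 109.

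**Stronger readings that the document does not support.** A reader might add that the 80% collapses in the ITT analysis, that it falls if first-line eradication is only 90–95%, or that 96.2% is a second-line rate. The article openly labels 96.2% as per-protocol and does not promise 80% power in ITT. Any ITT figure needs a rule for counting dropouts that the article does not give and that may sit in a document not shown. The 90–95% range has no source in the article. The Discussion does cite the same reference, grouped with two others, for the statement that data "have shown a constant acceptable eradication success rate for bismuth-containing quadruple therapy as a 2nd-line regimen", but the source cannot be inspected and the grouped citation does not establish where 96.2% came from.

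**Conclusion.** The point holds as a mismatch between the named margin and the claimed power. On the plan's own inputs and equal true rates, 100 per arm is the sample size for non-inferiority at one-sided 2.5%. For two-sided equivalence within ±8 points it gives about 60% power with a 95% CI and about 75% with a 90% CI, by the normal approximation. A truly equivalent regimen would then miss the criterion about 4 times in 10 or about 1 time in 4, against the stated maximum of 1 in 5. Any true difference lowers the equivalence power further.

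A reader might infer that the trial has a declared equivalence objective with 60% power as a settled fact. The article does not go that far: it gives a margin, not a hypothesis, and leaves the interval level open. If non-inferiority was intended, the sample size and the 80% both stand under the normal approximation.

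**What to change.** Keep 100 per arm and correct section 2.6 in one of two ways:

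- **(a) Non-inferiority.** Call the 8% a non-inferiority margin for modified quadruple therapy, tested at one-sided 2.5%: the lower limit of the 95% CI for the difference (modified minus bismuth-containing) must lie above −8 points. State about 80% power in the PP set by the normal approximation. Name the interval method, because exact power is about 79% with Wald limits and about 69% with Newcombe limits.
- **(b) Equivalence.** Keep the term, state whether the 95% or the 90% CI must lie within ±8 points, and restate the power as about 60% or about 75% respectively.

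The cost is a rewording of section 2.6 and, under (b), a less favourable power figure. No extra patients are needed. Holding 80% power for equivalence would instead take about 135 (95% CI) or 109 (90% CI) per arm, an increase of 35 or 9 per arm, which the correction does not require.
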